## Abstract

**Background:**

Cervical dysplasia (cervical intraepithelial neoplasia (CIN)) is caused by Human Papillomavirus (HPV) and is most common in women of reproductive age. Current treatment of moderate to severe CIN is surgical. This procedure has potential complications, such as haemorrhage, infection and preterm birth in subsequent pregnancies. Moreover, 15% of women treated for high grade CIN develop residual/recurrent CIN or cervical cancer after surgical excision. Finally, 75–100% of patients with a residual and recurrent CIN 2–3 lesion are still HPV positive. They could possibly benefit from an alternative medical treatment, which aims to eliminate HPV.

The primary study objective is to evaluate the effectivity of imiquimod 5% cream compared to treatment with Large Loop Excision of the Transformation Zone (LLETZ) for recurrent/residual CIN.

**Methods/design:**

This study is a multicentre, non-inferiority randomized single blinded study. The study population consists of female patients with histological proven residual/recurrent CIN after previous surgical treatment. Four hundred thirty-three patients will be included in the Netherlands. The first 35 patients will be included in a pilot study to prove non-futility.

Included patients will be randomized to receive either 5% imiquimod cream or LLETZ treatment. Imiquimod will be inserted three times a week intravaginally for a period of 16 weeks using a vaginal applicator. Ten weeks after the end of imiquimod treatment a biopsy will be taken for treatment response. In case of progressive or stable disease a LLETZ will be performed. At 12 and 24 months after the start of treatment cytology will be taken for follow up. The LLETZ group will be treated according to the current guidelines. Throughout the study, HPV typing and quality of life will be tested.

**Discussion:**

Repeated LLETZ in women with residual/recurrent CIN lesions has complications. We would like to possibly offer alternative treatment in a selected group to avoid these risks. Moreover, we monitor treatment efficacy, side effects and long-term recurrence rates.

**Trial registration:**

Medical Ethical Committee approval number: NL 53792.078.15. Affiliation: Erasmus Medical Center.

Registration number ClinicalTrials.gov: NCT02669459, date of registration: 27th January 2016.

## Background

Cervical dysplasia is caused by Human Papillomavirus (HPV) and is most common in women of reproductive age. Cervical dysplasia is known to be a precancerous stage of cervical cancer, the fourth most common type of cancer worldwide in women [1]. Treatment of moderate to severe dysplasia is often still surgical and aimed at eliminating the affected part of the transformation zone [2]. There are different type of surgical treatments (Large Loop Excision of the Transformation Zone (LLETZ), knife cone biopsy and laser conisation), the success rate is approximately 90% [3]. Historically, moderate and severe dysplasia was treated with cold knife biopsy. Nevertheless, with deep cones, hemorrhage, infection and post procedure stenosis were reported [4]. LLETZ seems to be a good alternative. This procedure could be performed under local anesthesia, is cheaper, less painful and seem to have less short and long term morbidity. Risk of residual disease is the same compared to cold knife cone [5]. Therefore, LLETZ is the golden standard for treating cervical dysplasia nowadays.

Still, there is uncertainty about the effects of LLETZ on short and long term in terms of recurrence, fertility and future pregnancy outcomes. Since women diagnosed with CIN are usually at their reproductive age, the effects on future fertility and pregnancy are of concern. Women with a shorter time interval from LLETZ to pregnancy seem to have an increased risk for spontaneous abortion [6]. Furthermore, a recent study described a higher subfertility rate in patients who underwent cervical surgery [7] Finally, several studies show a higher risk on preterm delivery and low birth weight [6, 8–11]. Systematic review and meta-analysis reported on LLETZ for CIN confirm an increased rate of preterm delivery (<32wks RR 1.98, 95% CI 1.31–2.98; <28wks RR 2.33, 95% CI 1.84–2.94), premature rupture of the membranes (RR 1.88, 95% CI 1.54–2.29) and low birth weight (< 2500 g RR 2.48, 95% CI 1.75–3.51) [8, 10]. One study reported a 10 fold higher risk for preterm deliveries after more than one conisation procedure in women with cervical dysplasia [12]. The risk of preterm birth could also be related to the volume of the cervical excision [13, 14]. However this research is performed in patients with one procedure, volume could be the same factor in patients with multiple procedures.

Apart from reproductive arguments there is an ongoing debate on the long-term outcome after treatment with surgical excision. Several studies show a recurrence rate of CIN 2–3 after treatment of 15–22% within 2 years [15]. Margin involvement seemed to be a risk factor for developing residual or recurrent cervical dysplasia [15]. Moreover, even after adequate treatment and follow up with normal smear results, patients who were treated for cervical intraepithelial dysplasia seem to have an excessive risk of cervical cancer compared to patients with normal primary smear test results [16, 17]. This risk is even almost 25 times higher in patients with abnormal smear test results than in patients with normal smear test results after treatment [18]. Recent studies found that most women with residual or recurrent disease test positive for HPV after treatment [19, 20]. Possibly this could be a tool for risk stratification in the follow up after treatment. Moreover, treatment failure could be related to the HPV status. This could raise the question if patients of this specific group could benefit from a non-invasive treatment modality to treat HPV and avoid further surgical treatment.

A potential agent in non-invasive therapy is imiquimod cream. Imiquimod 5% cream is a topical immune response modifier with indirect antiviral and antitumor properties. It is prescribed for HPV-associated genital warts, superficial basal cell carcinoma and actinic keratosis. Studies showed that it is a safe and effective treatment for usual type vulvar intraepithelial neoplasia (VIN), which is pathophysiologically comparable to CIN [21]. Furthermore, imiquimod seems also to be effective in primary CIN lesions [22]. It would also be helpful to determine a model to predict the responders to imiquimod therapy. This could select patients for non-ablative treatment.

The Topic 2 trial is a single blinded, randomized controlled trial with two intervention arms, in which imiquimod treatment is compared to standard treatment by LLETZ in patients with residual/recurrent CIN lesions after previous ablative treatment. The aim of the study is to investigate whether topical applied imiquimod is effective in the treatment of residual and recurrent CIN lesions.

## Methods

### Setting and study population

Patients are recruited at the moment in the Erasmus Medical Center, Rotterdam and in the Meander Hospital, Amersfoort, The Netherlands. This takes place at the outpatient clinic of gynecology. When non futility is proven after the pilot study, we intend to carry out a multi-center trial in the future throughout the Netherlands. Patients can be included if they have histologically confirmed residual or recurrent CIN lesions (CIN 1–3) after previous ablative treatment at least 6 months before the current diagnosis and have an age above 18 years. They are excluded if they have adenocarcinoma in situ, a history of (micro-) invasive cancer, hypersensitivity to the substance, immunodeficiency, pregnancy or lactation and insufficient knowledge of the English or Dutch language.

### Study objectives and outcome measures

The primary study objectives are:To evaluate the effectivity of vaginal application of imiquimod 5% in the treatment of recurrent or persistent CIN. The primary outcome measure is reduction to normal cytology of the cervix at 26 weeks after start treatment in imiquimod and LLETZ group.

Secondary study objectives and outcome measures are:To evaluate the effectivity of vaginal application of imiquimod 5% in the treatment of recurrent/residual CIN; reduction to absence of dysplasia in histology at 26 weeks as compared to baseline in the Imiquimod group.Evaluate of the effect of treatment on HPV DNA positivity of CIN lesions, by comparison of PCR HPV-DNA detection at cervical biopsies/cytology taken at 0 and 26 weeks.Establish the incidence and severity of side effects of LLETZ and imiquimod therapy.Review the Quality of life (QoL) in patients at 0 and 20 weeks and after 1 year by the following QoL questionnaires: RAND 36, QLQ-C30 and QLQ-CX24.Estimate the long term recurrence rate of CIN lesions measured by reduction to PAP1 by cytology examination at 6, 12 and 24 months after treatment. We will request the first outcome taken by the Dutch screening program for cervical cancer: cytology or HPV status will be obtained.

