### Data collection

The coded data will be stored both on paper and in an electronic database. A digital case report form (e-CRF) is used. The data is accessible only to the principal and coordinating investigator. The following data are recorded:

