#### 6 weeks follow-up

Adverse effects of imiquimod treatment: patient reported side effects and side effects noticed at clinical investigation.Adverse effects of LLETZ treatment: patient reported side effects.

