#### 10 weeks follow-up

Treatment compliance: amount of applied doses of imiquimod for the imiquimod group.Adverse effects of imiquimod treatment: patients reported side effects and side effects noticed at clinical investigation.Colposcopy with biopsies to determine progressive or invasive disease in the imiquimod group.

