#### 16 weeks follow-up

Adverse effects of imiquimod treatment: patient reported side effects and side effects noticed at clinical investigation.

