##### LLETZ group

Cervical cytology and HPV genotype.Quality of lifeWith abnormal PAP smear, determination of grade of cervical dysplasia.

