#### 12 and 24 months follow-up

Cervical cytology outcomes for all treatment groups, including HPV genotyping.

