## Discussion

The development of a non-surgical treatment modality for residual and recurrent CIN lesions will lower the amount of LLETZ procedures for this indication and complications as a result of surgical intervention. Evidence shows that 15–22% of high-grade CIN lesions will persist or recur after 2 years and that patients after treatment for high grade CIN lesions will remain at higher risk for cervical cancer in the future. Based on earlier studies, we hypothesize that at least 50% of patients with high grade CIN will benefit from immunotherapy with imiquimod. The current study aims to test the treatment effectivity, while also assessing the clinical applicability of imiquimod treatment by documentation of side effects and quality of life associated with treatment.

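### Quality of life is defined at 0 weeks, 20 weeks and 1 year but listed for collection at baseline and 26 weeks only, so no post-baseline time point is in both schedules

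*Protocol article*

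**What the plan says.** Under Study objectives and outcome measures, the protocol article lists as a secondary objective "Review the Quality of life (QoL) in patients at 0 and 20 weeks and after 1 year by the following QoL questionnaires", and names RAND 36, QLQ-C30 and QLQ-CX24.

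The Data collection section introduces a visit-by-visit list with "The following data are recorded". QoL appears in it at baseline for both groups and again at 26 weeks in each arm. The 26-week entry for the LLETZ group reads "Quality of lifeWith abnormal PAP smear, determination of grade of cervical dysplasia" (two list items run together in the text). The entries at 6, 10 and 16 weeks cover side effects, with compliance and colposcopy added at 10 weeks. There is no 20-week entry. The entry for 12 and 24 months is, in full, "Cervical cytology outcomes for all treatment groups, including HPV genotyping".

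Two other places bear on the point. The methods part of the abstract says that QoL is tested over the whole course of the study, without naming a week. The Discussion says that clinical applicability will be assessed by "documentation of side effects and quality of life associated with treatment".

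**The concern.** This is a disagreement between two explicit schedules in one document; it is not a detail left to a fuller protocol or to an analysis plan. Assessment times decide which questionnaires are handed out, and no analysis plan can recover a questionnaire that was never given. The article also foresees expansion from two hospitals to a multicentre trial, so a site that works from one section would collect different data from a site that works from the other.

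The 1-year point is the more costly one to lose. Under Interventions, women in the imiquimod arm with persistent or progressive disease at 26 weeks go on to surgical excision. If QoL collection ends at that visit, the effect of this later surgery on QoL is not measured, although the analysis is by intention to treat.

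A second and separate matter is that both schedules leave the treatment period without a questionnaire, while the Discussion ties QoL to treatment.

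**Working it through.** The check is a comparison of time points; there is no planned figure to reproduce. Weeks are counted from the start of treatment, as the article does for the primary outcome, and 1 year and 12 months are taken as week 52.

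| Time | In the QoL objective | QoL in the collection list | What the collection list has |
|---|---|---|---|
| Baseline (0) | yes | yes, both arms | patient characteristics, HPV genotype, QoL |
| 6 weeks | no | no | side effects, both arms |
| 10 weeks | no | no | compliance, side effects, colposcopy (imiquimod) |
| 16 weeks | no | no | side effects (imiquimod) |
| 20 weeks | yes | no | no such contact |
| 26 weeks | no | yes, both arms | cytology, HPV genotype, QoL and others |
| 12 months | yes | no | cytology, HPV genotyping |
| 24 months | no | no | cytology, HPV genotyping |

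**Step 1, overlap.** Defined: {0, 20, 52}. Collected: {0, 26}. The intersection is {0}. Defined but not collected: {20, 52}, which is 2 of 3 points. Collected but not defined: {26}. No post-baseline point is in both sets.

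**Step 2, the two mismatches differ in kind.** For week 20 there is no contact at all, and a different week is listed. For 1 year the contact exists, and QoL is absent from its entry.

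**Step 3, on-treatment coverage.** Imiquimod runs from week 0 to week 16. Neither set contains a point after week 0 and up to week 16. The first post-baseline point falls 20 − 16 = 4 weeks after the end of imiquimod under the objective, and 26 − 16 = 10 weeks after it under the collection list. The 6-week entry does exist for both arms; for LLETZ it is "Adverse effects of LLETZ treatment: patient reported side effects".

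**Step 4, what the 1-year point would capture.** The sample size section assumes 60% regression on imiquimod with 174 evaluable women per group. If every woman without regression had excision after the 26-week visit, that would be (1 − 0.60) × 174 = 69.6, or about 70 women. This is an illustration under the plan's own assumption, and it treats non-regression as equivalent to the biopsy finding that leads to excision.

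**The case against.** The strongest reply is that the collection list in a condensed article need not be complete, and the article itself shows that it is not. The first result from the national screening programme is to be requested under the objectives, yet no collection entry mentions it. CIN grade is an adjustment variable in the statistical methods, yet the baseline list does not name it. The abstract's general statement on QoL also leaves room for more questionnaires, perhaps sent outside visits. This stands to the extent that the loss of the 20-week and 1-year data is conditional on sites following the list. It does not remove the disagreement: the list gives a specific post-baseline week for QoL in both arms, and it is not the week in the objective. A statement that names no week cannot decide between them.

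A reader might infer that the QoL outcome cannot be analysed at all. The documents do not support that. Even on the strictest reading, baseline and 26-week questionnaires exist in both randomised arms, so a post-treatment comparison remains possible; what fails is its match to the outcome as defined.

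A reader might also infer that measuring QoL only after imiquimod has ended makes imiquimod look better tolerated. That is not shown either. LLETZ is a single procedure, and its early burden is missed too; at 20 or 26 weeks the LLETZ arm is further from its treatment than the imiquimod arm. Tolerability is also not left to QoL: at 16 weeks, for example, the list has "Adverse effects of imiquimod treatment: patient reported side effects and side effects noticed at clinical investigation", with similar entries at 6, 10 and 26 weeks, and a between-arm test of side effects is planned.

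Finally, the absence of an on-treatment questionnaire is not a contradiction. Both schedules agree on it, and the Discussion does not promise measurement during treatment. It can be raised only as an improvement.

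**Conclusion.** The inconsistency is real and should be corrected. Of the three time points at which QoL is defined, two have no collection entry, and the one post-baseline point that is collected is not part of the definition. If the collection list governs practice, the 20-week and 1-year QoL outcomes will not be available as defined. That conclusion rests on the list being what sites follow, which the wording that introduces it suggests but which a condensed article cannot prove.

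The documents do not show whether 20 or 26 weeks is the intended time. The matter concerns one secondary outcome and leaves the primary outcome, the non-inferiority margin, the sample size and the interim rule untouched.

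The lack of any questionnaire during the 16 weeks of imiquimod or soon after LLETZ is a separate, lesser design weakness. It holds under either schedule and would remain after the two schedules are aligned. The direction of any resulting bias is not established.

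**What to change.** Reconcile the QoL objective with the Data collection section into one schedule that applies to both arms.

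- The simplest version is baseline, 26 weeks and 12 months. Change 20 weeks to 26 weeks in the objective, since the 26-week visit exists and already lists QoL, and add QoL to the 12-month entry.
- If 20 weeks is the intended time, keep it in the objective and add a 20-week questionnaire for both arms to the collection list; QoL at 12 months is still to be added. This choice keeps the first post-treatment measure nearer to the end of imiquimod (4 weeks rather than 10) but needs a contact that is not now listed.
- As a separate improvement, give the same three questionnaires at the existing 6-week contact in both arms. This would place one measure within imiquimod use and soon after LLETZ, in line with the aim in the Discussion.

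The cost is wording in two sections and, in the simplest version, one or two extra questionnaire rounds at contacts already planned. The downside is a small added burden on patients. The reconciliation should be made before the multicentre expansion, because missed questionnaires cannot be collected afterwards.

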### Interventions

Patients will receive verbal and written information about the study procedure. They have to sign an informed consent, where after patients are randomized into the intervention arm or the standard treatment:Intervention arm: Imiquimod treatment. Patients in this group have to insert imiquimod 5% cream intravaginally for 16 weeks.Standard treatment. A LLETZ procedure is performed according to the current guidelines.

Patients in the imiquimod treatment group will apply imiquimod 5% cream intravaginally during 16 weeks. One sachet contains 12,5 mg of imiquimod and is applied with a vaginal applicator. The application frequency is 3 times a week. Patients get instructions and administer the cream themselves, before bedtime. The patients are advised to take an intravaginal shower with an applicator the next morning in order to remove cream leftovers, followed by an external shower to remove any remains on the vulva. Anti-inflammatory drugs (paracetamol or NSAID) can be used in case of mild systemic drug-related side effects. If the local or systemic side effects persist or are severe, patients are advised to reduce the frequency of the imiquimod insertion, first twice weekly, subsequently once weekly. Imiquimod treatment is discontinued for maximum of a week in case of persistent side effects. In order to prevent pregnancy, patients are advised to use adequate contraception. Subjects should refrain from vaginal sexual intercourse during the nights that imiquimod is applied until the vaginal shower the next morning. After 10 weeks a colposcopy is performed to rule out disease progression. Biopsies are only performed in case of suspicion of invasive disease.

In the standard treatment group, patients will undergo a LLETZ procedure within 4 weeks after the diagnosis. Excision of macroscopic lesions and the transformation zone will be achieved by a monopolar loop electrode, preferably under local anaesthesia.

Treatment efficacy is evaluated at 26 weeks follow-up for both groups. The Imiquimod group will have a Pap smear and a colposcopy with diagnostic biopsies. Biopsies are performed at the initial CIN lesion site and at any other suspect site, with a minimum of two. In case of persistent or progressive disease, surgical excision is performed. The LLETZ group will have follow-up with cervical smears at 6, 12 and 24 months according to the current guidelines.

This study protocol is almost identical to the TopIC-2 study, which is from the same study group. The TopIC-1 study studies the treatment of primary high grade CIN lesions with imiquimod or LLETZ procedure [22].

### Sample size calculation

The regression rate of a second LLETZ procedure is estimated 63% in a retrospective cohort (data not published). The regression rate of CIN lesions after treatment with imiquimod was based upon the only study reporting on the regression rate after 16 weeks of imiquimod therapy of primary CIN. This study showed a regression rate of 73% in patients with primary CIN lesions [23]. Since the effect could be lower in patients with residual or persistent CIN, we estimated the regression rate to be 60%.

To calculate the required sample size in this two-proportions non-inferiority trial we assume that the probability of regression is 63% for the standard (LLETZ procedure) while it is 60% after treatment with imiquimod.

Using a non-inferiority margin of 10% for the difference in proportions and a significance level (alpha) of 5%, a sample size of 174 per group is required to obtain a power of at least 80%. Allowing for 20% loss to follow-up the total required sample size is 433.

Because the uncertainty in the assumptions an interim analysis for futility will be performed by the Data Monitoring Committee (DMC) as soon as the primary outcome is available for 35 patients. This interim analysis is based on predictive power. That is the predicted probability of being able to prove non-inferiority given the results at the interim analysis. When the predictive power at this point is below 20% the trial will be stopped due to futility. Of course the DMC can always stop the trial due to safety concerns. The trial will never be stopped prematurely for efficacy so no alpha-adjustment is made.

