### Statistical methods

Analysis will be done according to the intention to treat principle and the non-inferiority principle to show that imiquimod is not worse than an existing treatment (LLETZ). To investigate efficacy we will perform a per protocol analysis (although this is not the primary outcome of the study). The primary outcome is the difference between the probability of regression in the LLETZ and the imiquimod arms. The expected difference (LLETZ-imiquimod) will be calculated together with the 95% Aggresti confidence interval. If the upper bound of the interval lies below the non-inferiority margin of 10% non-inferiority of the imiquimod treatment is assumed to be proved. Logistic analysis of potential confounders (age at diagnosis, CIN grade, number of previous treatments, smoking, HPV-subtype) will be performed. Analysis will be based on intention to treat protocol.

The prevalence and severity of side effects of imiquimod and LLETZ treatment, as documented according to Common Terminology Criteria for Adverse Events guidelines, will be presented as proportions and means with 95% confidence intervals. Differences in the rates of overall side-effects and severe side-effects between the imiquimod and LLETZ groups will be tested with a chi-square test. Disease recurrence rates, defined by abnormal cervical cytology, after 6, 12 and 24 months will be evaluated in adequately treated patients by use of multiple logistic regression analysis, after adjustment for age at diagnosis, CIN grade, smoking sexual behavior and HPV subtype.

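### 174 per group gives 27–38% power under the stated 63% LLETZ versus 60% imiquimod, not 80%; the figure matches a 3-point difference entered with the wrong sign

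*Protocol article*

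**What the plan says.** All inputs are in the protocol article, under Sample size calculation and Statistical methods.

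- **Rates:** "we assume that the probability of regression is 63% for the standard (LLETZ procedure) while it is 60% after treatment with imiquimod".
- **Reason for the lower imiquimod rate:** a 73% regression rate had been reported in primary CIN, and the plan lowers it on purpose: "Since the effect could be lower in patients with residual or persistent CIN, we estimated the regression rate to be 60"%.
- **Margin and alpha:** "Using a non-inferiority margin of 10% for the difference in proportions and a significance level (alpha) of 5"%. Whether alpha is one-sided or two-sided is not said.
- **Result:** "a sample size of 174 per group is required to obtain a power of at least 80"%.
- **Total:** "Allowing for 20% loss to follow-up the total required sample size is 433".
- **Analysis:** "The expected difference (LLETZ-imiquimod) will be calculated together with the 95% Aggresti confidence interval". Non-inferiority is concluded under this condition: "If the upper bound of the interval lies below the non-inferiority margin of 10"%.

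**The concern.** The analysis takes the difference as LLETZ minus imiquimod and asks whether its upper limit is below +10 points. The planning assumption puts the true difference at +3 points, against imiquimod. The assumed deficit therefore uses up part of the margin, and only 10 − 3 = 7 points remain for sampling error. A size of 174 per group looks far too small for a 7-point distance when the regression rates are near 60%.

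At stake is the power of the primary comparison. If the planning assumptions are exactly right and power is well below 80%, the most likely outcome is failure to show non-inferiority. Set against a stated power of 80%, that result could be taken as evidence against imiquimod when it is merely inconclusive.

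**Working it through.** **Inputs.** LLETZ 0.63, imiquimod 0.60, margin 0.10, power 80%, equal groups. Alpha is taken both as one-sided 5% and as one-sided 2.5%; the latter matches the 95% interval in Statistical methods, read as two-sided.

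**Formula** (unpooled normal approximation):

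n per group = (z₁₋α + z₀.₈₀)² × V / d²

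V = 0.63 × 0.37 + 0.60 × 0.40 = 0.2331 + 0.2400 = 0.4731, and d is the distance from the assumed true difference to the margin.

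**Trying to reproduce 174 with the inputs as stated** (d = 0.10 − 0.03 = 0.07):

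- One-sided 5%: (1.645 + 0.842)² × 0.4731 / 0.07² = 596.9, so 597.
- One-sided 2.5%: (1.960 + 0.842)² × 0.4731 / 0.07² = 757.8, so 758.
- Other methods, at one-sided 5% and 2.5%: pooled variance 598 and 759; Farrington-Manning 594 and 754; continuity-corrected 626 and 787.

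None is near 174.

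**With no true difference** (63% in both arms, V = 0.4662, d = 0.10): 289 at one-sided 5% and 366 at one-sided 2.5%. So 174 is too small even if imiquimod is exactly as good as LLETZ.

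**With the difference reversed** (imiquimod 63%, LLETZ 60%, d = 0.10 + 0.03 = 0.13):

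- One-sided 5%: 6.183 × 0.4731 / 0.13² = 173.1, so 174. Power at 174 is 80.2%; at 173 it is 79.98%, so 174 is the first whole number to reach 80%.
- Total with 20% loss: 2 × 173.08 / 0.8 = 432.7, so 433. Starting from the rounded 174 would give 2 × 174 / 0.8 = 435.
- One-sided 2.5%: 219.7, so 220.

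The reversed sign at one-sided 5% therefore reproduces both published figures. Of the variants tried, it is the only one that gives 174.

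**Power at 174 evaluable per group.** Under 63/60 the standard error is √(0.4731 / 174) = 0.05214, and power = Φ(d / 0.05214 − z₁₋α).

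- One-sided 5%: Φ(1.342 − 1.645) = 0.381.
- One-sided 2.5%: Φ(1.342 − 1.960) = 0.268.
- Exact binomial enumeration with the Agresti-Caffo interval gives 0.384 and 0.268.

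| True rates (LLETZ / imiquimod) | One-sided 5% | Two-sided 95% interval |
|---|---|---|
| 63% / 60% (as stated) | 38% | 27% |
| 63% / 63% | 61% | 49% |
| 60% / 63% (sign reversed) | 80% | 70% |

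**If nobody is lost** (433 / 2, about 216 per group), power under 63/60 is still only about 44–45% or 32%.

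**Margin at which 174 would suffice under 63/60:** 0.03 + 2.487 × 0.05214 = 0.160 at one-sided 5%, or 0.03 + 2.802 × 0.05214 = 0.176 at one-sided 2.5%. The stated margin is 0.10.

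**The case against.** The strongest objection concerns the cause. The article does not show its calculation, and the full protocol is not at hand. The reversed sign is inferred from a numerical match, and that match also needs one-sided 5%. This stands: the diagnosis is very well supported, because one slip yields both 174 and 433, but it is not proven. The shortfall in power does not depend on it.

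A second objection is that alpha is ambiguous, so no single power figure is right. This stands in part, and both readings are given for that reason. Neither comes near 80%. With the reversed sign the two-sided 95% interval gives only 70%, so planning at one-sided 5% also fails to match the stated analysis.

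A third is that a journal article condenses its protocol and that the two rates may simply have been swapped in print. Condensing does not excuse a stated result that contradicts its stated inputs. A swap is unlikely, because each rate has its own rationale: 63% from a retrospective cohort of second LLETZ procedures, and 60% as a deliberate reduction from 73%.

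A fourth is that the futility interim at 35 patients deals with uncertain assumptions. It works from the interim data and the planned final size, so it cannot restore power that this size does not provide. No claim is made here about how often it would stop the trial.

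**Conclusion.** The concern holds. Under the plan's own assumptions, 174 evaluable patients per group give 38% power at one-sided 5% and 27% with a two-sided 95% interval. If those assumptions are exactly right, the trial fails to show non-inferiority about 62% to 73% of the time. Power of 80% would need 597 or 758 per group, which with 20% loss is about 1,493 (2 × 597 / 0.8 = 1,492.5) or 1,895 (2 × 758 / 0.8) in total, against 433 planned.

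This rests on the stated rates, margin and direction of the test, equal allocation, and 174 evaluable per group. It does not depend on the choice of variance formula. It must be fixed, because the power stated for the primary comparison is wrong.

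**What to change.** Correct the Sample size calculation section:

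1. Delete the claim of at least 80% power for the 63/60 scenario.
2. State whether alpha is one-sided 5% or 2.5%, and make it agree with the interval in Statistical methods.
3. Give the power at 174 evaluable per group. With the two-sided 95% interval it is 27% under 63/60, 49% with both rates at 63%, and about 70% if imiquimod is 3 points better. At one-sided 5% the figures are 38%, 61% and 80%.
4. If a 3-point advantage for imiquimod was really intended, say so and justify it in place of the current rates.
5. State that a missed margin at this size is inconclusive and is not evidence that imiquimod is inferior.

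These changes cost only protocol wording and a less favourable stated power. They make the plan honest but leave the power as it is. The sponsor must still decide whether to enlarge the trial to the sizes given above, to justify different assumptions, or to continue at 433 with the low power declared. Enlarging would multiply recruitment by about 3.4 (1,493 / 433) or 4.4 (1,895 / 433).
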